### Control group

General practitioners of the control group are offered the same education sessions, but only after completing the follow-up data collection in both study arms. Control group patients receive treatment as usual.

Despite this sequential design, it cannot be excluded that study participation, 24-hour blood pressure measurement at baseline and follow-up, and completing a questionnaire at baseline and follow-up might influence the physicians’ and patients’ awareness for hypertension in both study arms.

### Pilot testing

The concept of this structured hypertension management for primary care, which is introduced during the education sessions, was developed in one exemplary teaching practice in our practice network. It combines guideline-based therapy, patient information on physical activity and diet, checklists for work-up of secondary hypertension, and patient supervision on blood pressure self-measurements according to standard. Patients were instructed about the documentation of blood pressure readings and how to react in case of blood pressure extremes. Patients with uncontrolled hypertension were scheduled for repetitive appointments to adjust the medications until blood pressure was in the target range or until other factors limited control. A phone recall to reschedule an appointment was performed for patients who had missed an appointment for blood pressure control. The retrospective evaluation of this hypertension management concept used in the model practice demonstrated that this strategy is effective: within one year blood pressure control rate of high-risk hypertensive patients increased from 46% to 74% [8] and for hypertensive patients in primary prevention, blood pressure control rate increased from 35% to 60% [9]. The results of the pilot testing are published separately [8,9].

### Sample size calculation

For the primary endpoint, a blood pressure control rate of 35% is assumed for the control group, while a blood pressure control rate of 70% is assumed for the intervention group [8,9]. Assuming an equal number of clusters per study arm, an average cluster size of five patients and an intraclass correlation coefficient of 0.05 [5], ten clusters per study arm are needed to detect the assumed effect using a chi-square test with a two-sided significance level of 5% and a power of 80%. Sample size calculation was performed in R package CRTSize, function n4props [10].

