### Inclusion and exclusion criteria for patients

Patients are eligible for recruitment if 1) they are ≥18 years old and 2) their blood pressure is uncontrolled according to current guidelines: ≥140/90 mmHg in office readings, and/or ≥130/80 mmHg in 24-hour ambulatory measurements (based on the average 24-hour blood pressure), and/or ≥135/85 mmHg in patient self-measurements at home (based on the mean of a one-week protocol with at least two measurements daily) [7]. Patients with and without hypertension-related diseases such as angiographically proven coronary disease, peripheral or cerebral vascular disease, and/or high risk conditions such as diabetes can be recruited. All patients must be able to give informed consent and to read and comprehend the German language. Patients fulfilling all of these criteria are asked for study participation, receive written information about the study, and sign an informed consent form. A total of 169 patients were enrolled at baseline; of these, 101 (59.8%) were associated with the intervention arm.

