### Outcome measures

The primary endpoint of the study is the change of the blood pressure control rate, defined as percentage of patients with an average 24-hour blood pressure <130/80 mmHg. The key secondary endpoints are the changes in average systolic and/or diastolic blood pressure (in mmHg) and changes in practice-specific hypertension management stratified by the intervention status of the practice. All outcomes are measured at baseline (before the intervention) and at follow-up (3 months after the last education session) in both study arms. This results in an average follow-up period of 5 months per patient.

To determine the interventional effectiveness on the patients’ level, each study patient receives a 24-hour ambulatory blood pressure monitoring at baseline and at follow-up. To control for confounding, general practitioners complete a questionnaire on medical characteristics of each study patient (for example, diagnosis, comorbidities, medication, and differential diagnoses). Study patients complete a self-administered paper and pencil questionnaire on individual characteristics such as sociodemographic characteristics, risk factors (for example, physical activity and smoking behavior), medication adherence, and management of blood pressure self-readings at baseline and follow-up.

At baseline, general practitioners complete a questionnaire on personal characteristics (age, sex), medical degree(s), additional qualifications, and individual attitudes toward hypertension treatment (motivation and self-efficacy). To determine practice changes after intervention, the follow-up questionnaire focuses on changes in daily practice routines and determines which of the hypertension management strategies are implemented by the practices.

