Cluster randomized trials from different countries evaluated various educational and organizational approaches to improve blood pressure control rates in primary care [15-24]. Most of these studies applied educational sessions for physicians and/or patients in combination with newly designed external support structures [15-22]. Three types of interventional approaches can be differentiated. The first category comprises patient-centered approaches, for example, used a clinical pharmacist led program [15,16] or electronic reminders on self-care to improve hypertension control [17]. A second category of studies evaluates physician-support structures, either by external study/audit centers or clinical pharmacists. These approaches span from feedback on pharmacotherapy by a pharmacist [18] to physician-pharmacist collaborations [19,20] to provider-specific audit reports with benchmarking elements [21] to physician-centered feedback with therapeutic recommendations by an external support structure to improve blood pressure therapy [22]. The effects vary from a mean group difference of +0.2 mmHg in systolic office blood pressure [22] to −10.3 mmHg in systolic 24-hour blood pressure [20] and from +0.04 mmHg in diastolic office blood pressure [21] to −4.6 mmHg in diastolic 24-hour blood pressure [19]. In comparison to these studies, only a few interventions aimed at internal practice redesign in addition to external support structures. Pouchain *et al*. introduced calibrated 24-hour blood pressure monitor devices in primary care practices, while Reuther *et al*. introduced strategies to organize hypertension management in primary care [23,24]. The mean group differences were −4.76/-1.88 mmHg [23] and −1.75/+0.14 mmHg [24]. In contrast to these studies, we are interested in redesigning primary care without external support structures addressing the physician manager in charge of the practice.

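### The planning effect of 35% versus 70% is attributed to the pilot reports, which the article itself gives as 46 to 74% and 35 to 60%; at those effects the planned 10 × 5 per arm has 61–78% power, and the enrolled sample largely restores it before attrition

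*Protocol article*

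**What the plan says.** Protocol article, Sample size calculation: "a blood pressure control rate of 35% is assumed for the control group, while a blood pressure control rate of 70% is assumed". The second rate belongs to the intervention arm, and the sentence cites the two pilot reports. The other inputs are equal numbers of practices per arm, five patients per practice on average, an intraclass correlation of 0.05, two-sided 5% and 80% power. The stated result is ten practices per arm.

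Protocol article, Pilot testing, on the same two references: "within one year blood pressure control rate of high-risk hypertensive patients increased from 46% to 74" percent in the first; in the second, for primary prevention, "blood pressure control rate increased from 35% to 60" percent. The section describes a retrospective evaluation in one model practice and mentions no control group.

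The trial itself differs from that setting. It compares two arms, recruits patients only if "their blood pressure is uncontrolled according to current guidelines", and follows them for a shorter time: "This results in an average follow-up period of 5 months per patient" (Outcome measures). According to the recruitment and eligibility sections, 24 practices were randomized equally and 169 patients enrolled, 101 of them in the intervention arm.

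**The concern.** The assumption and its cited source do not agree. The planned pair joins the starting rate of the primary-prevention pilot (35%) to an end rate that this pilot did not reach (60%) and that lies near the end rate of the high-risk pilot (74%). Neither group rose by 35 points, and no section says how 70% was obtained.

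This is not detail that a condensed article leaves to a fuller document, because both figures are printed and the second is offered as the basis for the first. The stated 80% power is what a reader will use to judge a non-significant result. If the design falls short of 80% at the effects its own sources showed, the reader should be told so, and told what power the enrolled sample has.

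**Working it through.** **Inputs from the article.** Planned: 10 practices × 5 patients = 50 per arm, intraclass correlation (ICC) 0.05, two-sided 5%. Enrolled: 12 practices per arm, 68 control and 169 − 68 = 101 intervention patients. Pilot effects: 46 to 74% and 35 to 60%.

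**Assumptions of mine.** Equal practice sizes within an arm. Loss to follow-up of 0, 10 or 20%, since the article gives no rate.

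**Formulas.** Design effect D = 1 + (m − 1) × ICC, where m is patients per practice. SE = √(p₁q₁D₁/n₁ + p₂q₂D₂/n₂). Power by the normal formula is Φ(|p₂ − p₁|/SE − 1.96). The t version uses the noncentral t with 2(k − 1) degrees of freedom for k practices per arm: 18 planned, 22 enrolled. A pooled-variance version lies between the two in every planned and enrolled case below.

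**Step 1: the plan's own figure.** D = 1 + 4 × 0.05 = 1.20, so the effective size is 50/1.20 = 41.7 per arm. For 35 versus 70% at 80% power, practices needed per arm are 6.7 (unpooled), 7.4 (pooled), 7.8 (t) or 8.9 (continuity-corrected), that is 7 to 9. The stated ten is therefore not reproduced at 80%. It matches about 90% power (9.8 pooled, 10.1 t). Ten is conservative for the stated assumption.

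**Step 2: power of the planned 10 × 5 per arm.**

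| Effect | SE | Difference/SE | Normal | Pooled | t, 18 df |
|---|---|---|---|---|---|
| 35 vs 70% | √(0.4375/41.7) = 0.1025 | 3.42 | 93% | 91% | 90% |
| 46 vs 74% | √(0.4408/41.7) = 0.1029 | 2.72 | 78% | 75% | 73% |
| 35 vs 60% | √(0.4675/41.7) = 0.1059 | 2.36 | 66% | 63% | 61% |

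For 80% power at the pilot effects, 46 versus 74% needs 11–12 practices per arm (13 with continuity correction), and 35 versus 60% needs 15–16 (17 with continuity correction).

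**Step 3: power of the enrolled sample.** Control: m = 68/12 = 5.67, D = 1.233, effective size 55.1. Intervention: m = 101/12 = 8.42, D = 1.371, effective size 73.7. Each range runs from the t version to the normal version. Under loss, both arms shrink equally and D is recomputed.

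| Effect | No loss | 10% loss | 20% loss |
|---|---|---|---|
| 46 vs 74% (28 points) | 89–91% | 86–89% | 83–86% |
| 35 vs 60% (25 points) | 79–83% | 76–80% | 72–76% |
| 35 vs 55% (20 points) | 60–64% | 57–60% | 53–57% |

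For example, 35 versus 60% with no loss has SE = √(0.2275/55.1 + 0.24/73.7) = 0.0859 and a ratio of 0.25/0.0859 = 2.91. Normal power is Φ(0.95) = 83%.

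**The case against.** **The trial that was run is larger than the one that was sized.** This stands. Before attrition, the enrolled sample reaches about 80% or more at both pilot effects. A reader might infer from 61–78% that the trial as conducted is badly underpowered, but those figures belong to the planned 10 × 5 design only.

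**The shortfall comes from the effect, not from too few practices for it.** This also stands. A reader might infer that 80% power holds only at 35 versus 70%. It does not: the planned design has 90–93% there and reaches 80% at about 35 versus 64–66%, or 46 versus 75–76%. Ten practices per arm absorbs part of the optimism, and 46 to 74% misses by only one or two points.

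**The 35% control rate may be wrong for patients selected as uncontrolled, but that does not by itself cut power.** Correct. With a lower control rate, the same 25 points are easier to detect: an illustrative 10 versus 35% gives 77–82% as planned and 94–95% as enrolled. The pilot rates also appear to include patients already controlled, so 25 and 28 points are what the cited sources showed, not forecasts for this trial.

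**Two further inferences are not supported.** The Discussion says of two practice-redesign trials: "The mean group differences were −4.76/-1.88 mmHg [23] and −1.75/+0.14 mmHg [24"]. A reader might turn these into control rates and find very low power. That needs a standard deviation the article does not give and ignores the diastolic half of the target. The article also does not say whether those differences are office or 24-hour readings. A reader might also argue that the pilot used phone recall and the trial does not. The list of printed and electronic tools omits recall, but the pilot section says its concept is introduced in the education sessions, so the omission does not show that recall was not taught.

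**Follow-up is complete, so nothing about enrolment can change.** True, and this limits the remedy to text and reporting. It does not remove the mismatch between assumption and source.

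**Conclusion.** The concern holds in this limited form. The planning effect is 35 points, while the reports cited for it are described as showing 28 and 25, from uncontrolled before-after data over one year in one practice. At those effects the planned design has 73–78% and 61–66% power instead of 80%.

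The consequence for the trial as enrolled is moderate. Power is good at 28 points even with 20% loss. It is borderline at 25 points, dropping below 80% once loss is allowed for, and inadequate at 20 points.

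These results rest on the article's ICC of 0.05, equal practice sizes within an arm, an analysis that accounts for clustering, and an assumed loss of 0–20%. The pilot reports are not at hand, so the comparison relies on the article's description of them. This should be corrected, but it does not undermine the design.

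**What to change.** 1. In Sample size calculation, give the pilot effects as 28 points (46 to 74%) and 25 points (35 to 60%) and say that they come from before-after data over one year in one practice. Then either justify 70% or label it an assumption not taken from the two reports.
2. Restate power for the enrolled sample (12 practices per arm, 101 and 68 patients, ICC 0.05) at 28 and 25 points and at a smaller effect such as 20 points, using the actual loss to follow-up.
3. Report the primary difference in control rates with a cluster-adjusted 95% confidence interval, so that readers can see which effects the data leave open.

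This costs a few sentences and one interval. No extra enrolment is required. The stated power becomes less favourable.

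### The stated inputs need 7 to 8 clusters per arm for 80% power (9 at most with one extra correction), not ten; ten clusters of five give about 90%

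*Protocol article*

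**What the plan says.** All the figures are in one paragraph of the protocol article, under Sample size calculation.

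- Control arm: "a blood pressure control rate of 35% is assumed for the control group".
- Intervention arm: "a blood pressure control rate of 70% is assumed for the intervention group".
- Clusters: "Assuming an equal number of clusters per study arm", with "an average cluster size of five patients" and "an intraclass correlation coefficient of 0.05".
- Test and error rates: a chi-square test with "a two-sided significance level of 5% and a power of 80" per cent.
- Result: "ten clusters per study arm are needed to detect the assumed effect".

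The paragraph names the software, R package CRTSize, function n4props. It mentions no continuity correction, small-sample correction, spare cluster, dropout allowance or variation in cluster size. Under Practice and patient recruitment the article reports that 24 practices were randomized to two equal arms, so 12 per arm.

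**The concern.** The paragraph reads as a complete calculation: every input to a standard two-proportion cluster formula is given, and ten is presented as the number required. A reader who puts the inputs in gets a smaller number, and one who starts from ten clusters gets a power well above 80%.

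At stake is whether the size justification can be reproduced. The target effect, the power and the number of clusters are the figures by which readers will judge a null or a positive result, and as printed all three cannot hold together without something further.

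**Working it through.** **Inputs**, all from Sample size calculation: p1 = 0.35, p2 = 0.70, difference d = 0.35, m = 5 patients per cluster, ICC = 0.05, two-sided alpha 0.05 (z = 1.960), power 0.80 (z = 0.8416).

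**Design effect:** 1 + (5 − 1) × 0.05 = 1.20.

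**Variance terms:** unpooled, 0.35 × 0.65 + 0.70 × 0.30 = 0.4375; pooled under the null, 2 × 0.525 × 0.475 = 0.49875.

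**Step 1. Try to reproduce ten.** Clusters per arm k = n × 1.20 / 5, where n is the individually randomized number per arm.

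- Unpooled: n = (1.960 + 0.8416)² × 0.4375 / 0.35² = 7.849 × 0.4375 / 0.1225 = 28.03. Then k = 6.73, so 7.
- Pooled under the null: n = (1.960 × √0.49875 + 0.8416 × √0.4375)² / 0.1225 = 30.75. Then k = 7.38, so 8.
- Pooled variance in both terms: n = 7.849 × 0.49875 / 0.1225 = 31.96. Then k = 7.67, so 8.

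Ten is not reproduced.

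**Step 2. Add one conservative correction at a time.**

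- t quantiles with 2(k − 1) degrees of freedom, unpooled: about 7.8, so 8. With either pooled form, between 8 and 9, so 9.
- Continuity correction, n′ = (n/4) × [1 + √(1 + 4/(n × 0.35))]²: unpooled 33.50, k = 8.04; pooled 36.24, k = 8.70; fully pooled 37.45, k = 8.99. All round up to 9.
- One spare cluster per arm: 7 + 1 = 8, or 8 + 1 = 9.

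No single correction exceeds 9.

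**Step 3. Power of ten clusters of five.** Effective n per arm = 50 / 1.20 = 41.67.

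- Unpooled: standard error √(0.4375 / 41.67) = 0.1025; 0.35 / 0.1025 = 3.416; Φ(3.416 − 1.960) = 92.7%.
- Pooled: Φ[(0.35 × √41.67 − 1.960 × √0.49875) / √0.4375] = Φ(1.323) = 90.7%.
- t with 18 degrees of freedom: 89.8%.
- Beta-binomial simulation: 91.2% for the chi-square test adjusted by the design effect, 88.0% for a t-test on cluster-level results.

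With the pooled formula, 7, 8, 9, 10 and 12 clusters of five give 77.8%, 83.2%, 87.5%, 90.7% and 95.0%. The 80% line is therefore crossed at eight.

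**Step 4. What would give ten.** Each of these reaches ten, and the article states none of them.

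| Route | Clusters per arm before rounding up |
|---|---|
| Continuity correction plus t quantiles, pooled | 9.59 |
| Continuity correction plus one spare cluster, pooled | 9.70 |
| Fully pooled variance, continuity correction, n rounded up first (38 × 1.20 / 5) | 9.12 |
| About 25% dropout, pooled (7.38 / 0.75) | 9.84 |
| 90% power, pooled | 9.76 |
| Intervention rate of 65% instead of 70%, unpooled | 9.52 |

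The last two routes change a stated input. The first four keep every stated input and add something.

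**The case against.** The best defence is that nothing printed need be wrong. The first four routes in the table reach ten at 35% versus 70% and 80% power. A journal article condenses a fuller protocol, in which a continuity correction or a dropout reserve would normally be recorded. The named function could not be run for this review, so its conventions and rounding were not checked.

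Much of this stands. A reader might infer that the power or the assumed rate must have been misreported, for example that the trial was really sized for 90% power or for an intervention rate near 65%. The document supports neither: both values come only from working backwards from ten, and the article states 35% and 70% plainly. The cause of the gap is unknown.

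What does not stand is that the sentence can therefore be left alone. It is not merely short of detail: it says ten clusters are needed for 80% power from a listed set of inputs, and those inputs do not lead there. Naming the software does not close the gap when no further setting is reported.

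It is also fair to say that the trial is unharmed. The discrepancy errs towards more clusters than required, 12 per arm were randomized, and the article's Trial status section reports that follow-up data collection is complete.

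**Conclusion.** The sample size statement is inconsistent as printed. On its own inputs 80% power needs 7 to 8 clusters per arm, or 9 with one added conservative correction. The overstatement is thus one to three clusters, or 50 patients per arm against 35 to 45. Ten clusters of five give about 90% to 93% power by the standard formulas (89.8% with t quantiles), some 10 to 13 points above the stated figure.

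Either a stated input was not the one used, or an unreported correction or reserve was added. The document does not allow a choice between these, and it should not be read as proof that a particular input is false. Nor does the point suggest an underpowered trial: under the stated assumptions the power is higher than claimed.

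The result takes the 35% and 70% rates, the ICC of 0.05 and equal clusters of five as given, and does not judge whether they are realistic. It is a reporting error worth correcting, with no bearing on conduct.

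**What to change.** Re-run the calculation, report the exact function call, and restate the sentence so that inputs, cluster number and power agree. Two forms would do.

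1. Keep ten clusters of five and give the power they deliver at the stated inputs, about 90%, naming the variance formula or correction used.
2. Keep 80% power, give the 7 to 8 clusters required (at most 9 with one named correction), and state the correction, spare cluster or dropout allowance that raised the number to ten.

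If the records show that a different input was used, report that input from the records. Do not insert an intervention rate chosen because it happens to yield ten.

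The cost is one re-run and one corrected sentence, which can go in a correction or in the results paper. Randomization, data collection and analysis are unchanged.

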### Quality control procedures

Quality controls are conducted during all study phases. After recruitment, physicians’ and patients’ inclusion criteria are controlled. Consent forms are checked for completeness. After baseline and follow-up data collection, quality controls are conducted to assure that required data collection documents are complete. Baseline and follow-up data of each study patient are checked using birth date to ensure that data are merged correctly.

The data are entered manually in an electronic database with restricted access. To control for input errors, 10% of the data are entered twice. An error rate of 5% is accepted; otherwise all values are entered twice. The data are checked for plausibility using simple frequencies.

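### The 5% entry-error tolerance makes no exception for the 24-hour blood pressure means that decide the primary endpoint, and its denominator is not stated; verifying those few values in full is a cheap improvement

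*Protocol article*

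**What the plan says.** The section *Quality control procedures* of the protocol article describes the entry process in four statements. Staff key the data by hand into a database. The threshold that triggers complete double entry is given as "An error rate of 5% is accepted; otherwise all values are entered twice". The sample on which that threshold is judged is described as "To control for input errors, 10% of the data are entered twice". Beyond double entry, the only look at the entered values is a review of their distributions: "The data are checked for plausibility using simple frequencies".

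It also provides for checks that documents are complete and that each patient's baseline and follow-up records are merged correctly, using date of birth. It names no separate rule for any variable.

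Under *Outcome measures*, the primary endpoint is the change in the control rate, "defined as percentage of patients with an average 24-hour blood pressure <130/80 mmHg". The same section sets out when the pressure is recorded: "each study patient receives a 24-hour ambulatory blood pressure monitoring at baseline and at follow-up". Each patient's status at a visit therefore rests on two entered numbers, and on four if both visits count. *Trial status* reports that data management, including quality control, was still under way when the article was written.

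**The concern.** A 5% tolerance may be acceptable for lifestyle or attitude items, where one wrong answer has little influence. It is loose for two numbers per visit that are compared with a cut-off to decide the primary endpoint, and that also feed the t-tests on mean pressure.

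If the double-entered tenth passes, the remaining 90% is entered once and never compared with anything. The other checks do not fill this gap. Frequencies expose impossible values, but not a systolic mean of 128 keyed as 138 or a diastolic mean of 79 keyed as 89. Completeness checks and the date-of-birth check do not look at the pressure values at all.

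Errors unrelated to study arm would misclassify some patients in both arms, pull the difference in control rates towards zero and cost some power. Because the 5% has no stated denominator, it is also unclear what level of error the rule tolerates.

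**Working it through.** The article derives no figure from the 10% and 5% rules, so there is none to reproduce. The check asks what the tolerance would mean for the endpoint.

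**Inputs from the protocol article.** Accepted error rate 5% and double-entered share 10% (*Quality control procedures*); two values per visit and two visits (*Outcome measures*); 169 patients, 101 of them in the intervention arm (*Inclusion and exclusion criteria for patients*); 24 practices in two equal arms (*Practice and patient recruitment*); control rates of 35% and 70%, ten clusters of five per arm, intraclass correlation 0.05, two-sided 5% level (*Sample size calculation*).

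**Assumptions, not in the article.** Errors occur at the tolerated rate, are independent between values and do not depend on arm. The share of affected patients whose control status changes is varied from 10% to 100%.

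**Step 1: patients with at least one wrong value.** With error rate e per value and m values, the share is 1 − (1 − e)^m.

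| Reading of the 5% | 2 values (one visit) | 4 values (both visits) |
|---|---|---|
| Error rate per entered value, e = 5% | 1 − 0.95² = 9.75% | 1 − 0.95⁴ = 18.5% |
| Disagreement rate between two entries, e = 1 − √0.95 = 2.53% | 5.0% | 9.75% |
| Counted per patient | 5% | 5% |

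The range is about 5% to 19%.

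**Step 2: how much the sample shows.** Suppose the 10% means about 17 of the 169 patients, that is 34 follow-up values. One error (1/34 = 2.9%) passes. The exact one-sided 95% upper limit for the error rate is then 13.2% per value. Passing therefore does not show that the true rate for these values is below 5%.

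**Step 3: from wrong values to wrong endpoints.** If a fraction w of patients has a wrong value and a fraction f of those changes status, equally in both arms, the observed difference is 35 × (1 − 2wf) points. Power at the planned size uses the normal approximation for two proportions, with 50 patients per arm divided by the design effect 1 + (5 − 1) × 0.05 = 1.2, that is 41.7 per arm. With w = 9.75%:

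| Share changing status (assumed) | Difference (points) | Power, 10 clusters of 5 per arm |
|---|---|---|
| 0% | 35.0 | 90.7% |
| 10% | 34.3 | 89.5% |
| 25% | 33.3 | 87.5% |
| 50% | 31.6 | 83.6% |
| 100% | 28.2 | 73.9% |

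**Step 4: power at the enrolment reported.** With 12 practices per arm, the mean cluster sizes are 101/12 = 8.4 and 68/12 = 5.7. The design effects are 1 + 7.42 × 0.05 = 1.37 and 1 + 4.67 × 0.05 = 1.23, and the effective sizes 101/1.37 = 74 and 68/1.23 = 55. The same approximation gives power of about 98% with no error and about 90% if all of the 9.75% change status (99% and 91% with the unpooled variance). With an assumed 20% dropout, that extreme case still gives about 84%.

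**Step 5: size of the remedy.** 169 patients × 2 visits × 2 values = 676 numbers, fewer if some patients have no follow-up reading.

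**The case against.** The strongest reply is that entering a sample twice, with a preset trigger for entering everything twice, is a coherent procedure that contradicts nothing in the article. The 5% is a trigger, not an expected error rate, and nothing suggests that errors run near it. The practical consequence is also small: on the planning assumptions, realistic misclassification costs a point or two of the difference, and the enrolment reported leaves ample power. All of this stands, and it sets the size of the point.

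It can also be said that a journal article condenses, and that a tighter rule for outcome fields may exist in a fuller document. That is possible, and one sentence would then settle the matter. But the article does not merely omit detail. It prints an acceptance rule for the data in general, with a fallback covering all values, and exempts nothing.

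Two stronger readings are tempting and are not supported:

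- A reader might infer that up to one patient in ten has a wrong primary endpoint. The 9.75% follows from only some readings of an undefined percentage, it is not a maximum, and it counts wrong values rather than misclassified patients. The 28-point difference requires every affected patient to change status.
- A reader might infer that errors which are found stay uncorrected. The section does not say what happens to discrepancies in the double-entered tenth when the rate is 5% or lower. What does follow is that errors in the single-entered 90% go unseen once the sample passes.

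**Conclusion.** The point holds as a minor one. The printed rule gives the endpoint-defining values no more protection than any questionnaire item, and it leaves the 5% without a denominator. The remaining checks would not catch a plausible wrong value near the cut-off.

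The likely consequence is slight dilution, not a threat to the trial's conclusion. This rests on errors being unrelated to arm and on no more than about half of the affected patients changing status, neither of which the article can confirm. If the true effect is smaller than the 35 points planned, the margin in power is smaller too. The case for acting is that the dilution is avoidable at almost no cost.

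**What to change.** In *Quality control procedures*, state three things:

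1. All baseline and follow-up 24-hour systolic and diastolic means, with study arm and practice, are entered twice, and every discrepancy is resolved against the source record.
2. The 10% sample and 5% tolerance apply to the remaining questionnaire fields only.
3. The 5% is counted per value.

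The cost is a few hours of re-keying (at most 676 pressure values, plus arm and practice) within data management that the article describes as ongoing. It needs no new staff or procedure. If a stricter rule for these values already exists elsewhere, a sentence saying so is enough.
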